### Sample size

The sample size was calculated on the basis of the primary outcome. To the best of the our knowledge, at the time of study development there was no published data reporting quadriceps strength following tourniquet use and total knee replacement that could be used to estimate a sample size for this study. Therefore, allowing for a medium to large effect size (Cohen’s d = 0.65), based on the large quadriceps function differences between groups observed by Liu et al. [16] which were measured using surface electromyography, a two-sided significance level of α = .05 and power of 80%, a minimum sample size of 39 participants per arm was estimated. Allowing for a 15% drop-out rate, we aimed to recruit 45 participants to each group.

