## Methods

### Study design

The study is a single centre, parallel-arm, double-blinded (participant and assessor), randomised trial with 1:1 random allocation. The study schedule is summarized in Table 1.

**Table 1 Tab1:** Study schedule

	Pre-randomisation	Surgery Day 0	Post-surgery				
			Day 2	Day 5	During inpatient stay	3 months	12 months
Enrolment							
Eligibility screen	X						
Informed consent	X						
Randomisation		X					
Interventions							
Tourniquet TKR		X					
No tourniquet TKR		X					
Assessments							
Demographic variables	X						
Quadriceps strength	X		X	X		X	X
Blood loss and replacement		X			X		
Surgeon satisfaction		X					
Operation and anaesthetic time		X					
Tourniquet inflation time		X					
Pain			X	X			
Morphine equivalent daily dose					X		
Complications					X		
Knee Society Score	X					X	
Oxford Knee Score	X					X	X
WOMAC	X					X	X
EQ-5D-5 L	X					X	X
Revision surgery							X
Cement mantle							X

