### Randomisation

People who meet eligibility requirements and provide informed consent will be randomly allocated to either tourniquet or non-tourniquet groups with a 1:1 allocation ratio in blocks of 10. The allocation sequence will be computer generated by the research coordinator prior to trial commencement. Allocation will be concealed until immediately prior to anaesthetic induction, at which time the surgeon will access the allocation code for that participant via an opaque sealed envelope.

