### Statistical analysis plan

The main results will be based on intention-to-treat analysis which will include all participants as randomised. Per protocol analysis will also be conducted as secondary analysis and include only patients whose surgery was completed as randomised. All categorical data will be summarised using frequencies and percentages and baseline characteristics will be compared using the Chi-squared statistic. Interval or continuous data will be summarised using means with standard deviations or medians with lower and upper quartiles if the data are skewed. The amount of missing data for each group and each outcome will be described with frequencies and proportions. Analysis will include cases with available data. No imputation of missing data will occur. For questionnaire data, if a participant has not responded to ≥15% of questions in a questionnaire (or subscale where relevant), the responses for that scale will not be included in the analysis.

Linear mixed models [33] will be used for group comparisons of quadriceps strength at the different follow-up time points (2 days, 5 days, 3 months and 12 months). The major advantages of using this method are that it accounts for intra-individual correlations in observations, multiple variables can be included in the model and the method uses all available data even in the presence of unbalanced data. If assumptions permit, the restricted maximum likelihood approach will be adopted. The models will include an interaction term between time and treatment group, which will indicate the between group differences in quadriceps strength changes from baseline. The linear mixed model will also be considered for the analysis of continuous secondary outcomes that are available at multiple follow-up time points (> 3 time points). Other continuous outcomes that are only assessed at baseline and once/twice at follow-up will be analysed using linear regression, allowing for estimation of clustered sandwich error estimates [34]. Non-parametric models such as quantile regression will be considered for cases where assumptions of linear models are not satisfied.

Secondary outcomes that are categorical will be analysed using logistic regression models [35]. Count data such as hospital length of stay will be analysed using Poisson regression or other count-data models (e.g. negative binomial regression) if the assumptions of the Poisson regression models are not satisfied [36].

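### A target of 45 per arm does not quite keep the plan's own minimum of 39 per arm at the stated 15% drop-out, though planned power is essentially unaffected

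*Protocol article*

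**What the plan says.** The Sample size section of the protocol article bases the calculation on the primary outcome, the change in quadriceps strength at 3 months. Its inputs are a standardised difference ("allowing for a medium to large effect size (Cohen’s d = 0.65") and "a two-sided significance level of α = .05 and power of 80" per cent. From these, "a minimum sample size of 39 participants per arm was estimated". The next sentence moves from that minimum to the recruitment target: "Allowing for a 15% drop-out rate, we aimed to recruit 45 participants to each group". The section does not say how the drop-out allowance was applied.

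Two other sections bear on the point. Randomisation allocates "with a 1:1 allocation ratio in blocks of 10", so a total of 90 fills nine blocks. The Statistical analysis plan section analyses participants with available data and adds that "No imputation of missing data will occur".

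**The concern.** The section prints three linked figures: a minimum of 39 per arm, a drop-out rate of 15% and a target of 45 per arm. The third is presented as the number that secures the first at the second. A reader who takes 15% off 45 gets a number below 39, so the three cannot all hold as printed.

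What is at stake is modest. The drop-out allowance is the only protection that the sample-size statement offers for the 39. It is also the natural benchmark for judging attrition at 3 months once the trial reports. If it is overstated, a trial that loses exactly the planned 15% would appear to have kept its minimum when it had not.

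**Working it through.** **Inputs, all from the Sample size section except the allocation ratio.** Standardised difference d = 0.65; two-sided α = 0.05; power 80%; minimum 39 per arm; drop-out 15%; target 45 per arm. Allocation is 1:1 (Study design: "randomised trial with 1:1 random allocation").

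**Step 1: reproduce the 39.**
- Normal approximation: n = 2 × ((1.960 + 0.842)/0.65)² = 37.15 per arm, rounded up to 38.
- Two-sample t-test (noncentral t with 2n − 2 degrees of freedom and noncentrality d × √(n/2)): n = 38.14 per arm, rounded up to 39.

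The t-test gives the printed 39 exactly, so the base figure is sound and the question concerns only the drop-out step.

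**Step 2: apply the stated drop-out to the stated target.**
- Per arm: 45 × (1 − 0.15) = 38.25, which is 0.75 below 39.
- Both arms: 90 × 0.85 = 76.5, against 2 × 39 = 78.

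**Step 3: find the target that matches 15%.**
- 39/(1 − 0.15) = 45.88, so 46 per arm (92 in total).
- Check: 46 × 0.85 = 39.1, which meets 39.

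**Step 4: find the drop-out that 45 tolerates.**
- 45 − 39 = 6 losses per arm; 6/45 = 13.3%.
- A seventh loss (7/45 = 15.6%) leaves 38.

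**Step 5: see where 45 could have come from.**
- 39 × 1.15 = 44.85, rounded up to 45.
- 38/0.85 = 44.71, rounded up to 45, starting from the normal-approximation figure of 38, which the article does not print.
- 39/0.85 = 45.88, rounded down to 45.

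All three routes reach 45, and the article does not show which was used.

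**Step 6: size the effect on power (t-test, d = 0.65, two-sided 5%).**

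| Evaluable per arm | Power |
|---|---|
| 38 | 79.9% |
| 38.25 (expected at 15% drop-out from 45) | 80.1% |
| 39 (stated minimum) | 80.9% |

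The expected 38.25 lies below the rounded minimum of 39 but above the unrounded requirement of 38.14.

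**The case against.** The strongest reply is that nothing of substance is lost. The 39 is 38.14 rounded up, the expected 38.25 still exceeds 38.14, and power at that number is 80.1%. The gap is one participant per arm, about 2% of the target. It is far smaller than the uncertainty in d = 0.65, which the article says was borrowed from electromyography differences because no strength data were available. This stands, and it fixes the size of the point. It does not make the printed figures agree: the plan itself names 39 as the minimum, and 45 less 15% does not reach it.

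A second reply is that the primary analysis is a linear mixed model over four follow-up times. A participant lost after the inpatient stay would still contribute day 2 and day 5 strength, so a count of completers at 3 months understates the information available. That is a fair remark about the analysis. However, the sample-size calculation claims no gain from repeated measures, so the mismatch within it remains.

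A third reply concerns cause. A reader might infer that the authors multiplied by 1.15 where they should have divided by 0.85. The documents do not support stating this as fact, because no formula is given and 45 can be reached in other ways. The mismatch does not depend on the cause.

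Finally, the target is written in the past tense, and recruitment was expected to run for four years from October 2014, while the article appeared in December 2018. A new target would have little practical use, which favours restating the allowance over changing the number.

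**Conclusion.** The point holds as a small internal inconsistency. At the stated 15% drop-out, 45 per arm leaves 38.25, below the stated minimum of 39. The matching target would be 46, and 45 per arm supports an allowance of 13.3%.

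A reader might go further and infer that the trial is underpowered. The documents do not support that. On the plan's own inputs, power at 15% drop-out is about 80% (79.9% at 38 and 80.1% at 38.25 per arm), so the planned power is essentially kept. Design, analysis and interpretation are unaffected.

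The conclusion rests on the printed d, α and power, on a two-sample t-test (which reproduces the 39), and on reading the drop-out rate as the proportion of recruited participants without the 3-month primary outcome, equal in the two arms.

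**What to change.** Keep 45 per arm, which preserves nine complete blocks of 10, and restate the allowance in the Sample size section. For example:

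> 45 per arm retains the minimum of 39 for drop-out up to 13%; at 15% drop-out about 38 per arm remain and power is about 80%.

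If the 15% allowance is to stay as the basis of the target, the figure that matches it is 46 per arm, 92 in total, which does not fill whole blocks of 10. In either case, stating the inflation formula would remove the ambiguity.

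The cost of the restatement is one sentence and a slightly less favourable stated drop-out allowance. No extra participants are needed.

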### Ethics and dissemination

Barwon Health Human Research Ethics Committee, Geelong, Australia approved the study including the protocol and the participant information and consent form (reference 11/89). The Ethics Committee will be notified of any adverse events relating to the study or any changes to the study protocol. The study complies with the National Statement on Ethical Conduct in Research [38]. The study is registered with the Australian New Zealand Clinical Trials Registry (ref: ACTRN12618000425291) [39].

All investigators and the trial statistician will have access to the final dataset. Key study results will be shared with interested participants in writing using plain English. Results will be disseminated at national and international conferences and in peer-reviewed journals. Authorship eligibility for disseminated material will be determined according to international criteria [40].

## Discussion

Th current study will fill a knowledge gap and provide much needed empirical evidence regarding the effects of tourniquet use in TKR. The study results will assist orthopaedic surgeons when deciding on the most beneficial surgical technique for their patients.
